## Abstract

Depression and anxiety are the most prevalent mental health difficulties in the EU, causing immense suffering and costing the global economy EUR 1 trillion each year in lost productivity. Employees in construction, health and information and communications technology have an elevated risk of mental health difficulties. Most mental health interventions for the workplace have been targeted at larger companies and small and medium-sized enterprises (SMEs) are often overlooked despite most people being employed in SMEs. The MENTUPP intervention aims to improve mental health and wellbeing and reduce depression, anxiety, and suicidal behaviour. The MENTUPP project involves the development, implementation, and evaluation of a multilevel intervention targeting both clinical and non-clinical mental health issues and combating the stigma of mental (ill-)health, with a specific focus on SMEs. The intervention is underpinned by a framework of how to create a mentally healthy workplace by employing an integrated approach and has been informed by several systematic reviews designed to understand organisational mental health interventions and a consultation survey with key experts in the area. The intervention is facilitated through the MENTUPP Hub, an online platform that presents interactive psychoeducational materials, toolkits, and links to additional resources in an accessible and user-friendly manner. This paper presents the pilot study protocol for delivering the MENTUPP intervention in eight European countries and Australia. Each intervention country will aim to recruit at least 23 participants in 1–3 SMEs in one of the three high-risk sectors. The central aim of the pilot study will be to examine the feasibility, acceptability, and uptake of the MENTUPP intervention across the target SMEs. The findings will contribute to devising the protocol for a cluster randomised controlled trial (cRCT) of the MENTUPP intervention. Findings from this study will also be used to inform the optimisation phase of the MENTUPP intervention which will aim to improve the materials and the implementation of the intervention as well as enhancing the evaluation strategy which will be employed for the cRCT.

## 1. Introduction

A negative working environment may lead to occupational stress and subsequently, physical and mental health problems (including harmful use of substances or alcohol) [1,2]. Research indicates that occupational stress and mental health problems have been linked to absenteeism (the number of days unable to work), presenteeism (reduced ability to work productively and work performance), low employee satisfaction, and lost productivity [1,3,4,5]. Psychosocial stresses in the workplace, such as job uncertainty, emotional demands, poor social relationships, low job control, poor management, harassment and bullying, poor communication, and long working hours, have been shown to undermine mental health [2,6,7,8,9]. Depression and anxiety are the most prevalent mental disorders in the EU [10], costing the global economy EUR 1 trillion each year in lost productivity [11].

There is a strong association between depression and suicidal behaviour (suicide and self-harm), which is compounded by comorbidities, including anxiety and stress-related mental and physical health symptoms [12]. Additionally, it is well-known that depression often co-occurs with burnout and that they can develop simultaneously [13]. A systematic meta-review has indicated that there may be an association between a negative work environment and the development of work-related stress, depression, and anxiety [14]. Another recent meta-review of 72 literature reviews also showed a strong association between psychosocial factors with mental disorders, especially with regard to job strain, long working hours, and effort-reward imbalance [15].

In a systematic review of predictors for burnout, job demands, lack of job resources, lack of social support, social hindrance, poor organisational commitment, high work-family conflict, and poor communication may have harmful effects on occupational burnout [16]. Research has consistently shown that people in specific occupational sectors—construction and health—have mental health problems and an elevated risk of suicide, jointly representing up to 49% of male suicides and 26% of female suicides [17]. For example, research has indicated that doctors and nurses are more likely to experience burnout than other occupations because working overtime is commonplace in the profession [18] and employees who work excessive hours have poorer health overall compared to their counterparts [19]. This is further compounded by the specific emotional demands of the occupation [20]. Furthermore, employees in the construction sector are at increased risk of suicide [21,22,23] with male construction workers in the UK almost four times more likely to die by suicide than the general population [22,24]. Suicide in this sector has been associated with increased alcohol consumption, relationship issues, and poor help-seeking behaviours [25,26]. The construction sector is associated with specific workplace factors, such as high work demands and lack of job control [8,27], which is evident across the organisational structure with supervisors also experiencing high psychological stress [9]. In addition, employees working in the information and communications technology (ICT) sector are at increased risk of depression, comorbid stress related symptoms, and reduced wellbeing in comparison to other occupational sectors because of the high workload, ambitious work targets, and shift-work, associated with the sector [28,29]. Male-dominated workplaces, such as, e.g., the construction and ICT sectors, are also known to have high levels of stigma related to mental health and cultures which encourage self-reliance and stoicism, which may hinder help-seeking behaviour, thus increasing distress [30].

The healthcare, construction, and ICT sectors are associated with high levels of work-related stress, which has been linked to severe, negative psychological outcomes [15,31]. This has been further compounded by the mental health impacts of COVID-19 [32]. The pandemic has been associated with certain mental health issues such as anxiety, post-traumatic stress disorder and sleep disorders in healthcare workers, while factors such as job insecurity and long periods of isolation which are common in the construction and ICT sectors may worsen psychological distress [32].

Within the construction, health, and ICT sectors, employees and managers/owners of small to medium-sized enterprises (SMEs) may be at heightened risk of mental health problems. Many SMEs may have limited capacity to implement mental health promotion or occupational stress programmes [33] because they lack the expertise, knowledge, and budget to implement health promoting programmes [34]. Moreover, they can face specific challenges which employees and managers/owners in larger enterprises may not face including social isolation, long work hours, reluctance to introduce new and safer practices and technologies, unhealthier work environment, lack of human resource management systems, and financial pressures [35,36]. Given that 94% of all enterprises in the European Union are classified as small to medium-sized, SMEs present an ideal opportunity to implement a mental health intervention that promotes mental wellbeing, prevents the development of mental health problems, and tackles stigma associated to mental health.

Workplaces can be a source of well-being [4] and individual employee mental health is inextricably linked to the organisational psychosocial workplace environment [37]. Supportive workplace environments have been linked to lower levels of job dissatisfaction, burnout, and depression [38,39]. Programmes that educate and encourage peer support have been shown to be successful in encouraging help-seeking outcomes [40,41]. Workplaces that promote mental health awareness, de-stigmatise mental illness, and support people with mental disorders are more likely to reduce levels of depression, absenteeism, presenteeism, and increase productivity, and are more likely to benefit from associated economic gains [42,43,44]. Research has shown that improving access to evidence-based interventions for minor stress-related depressive symptoms in occupational sectors associated with high suicide rates may prevent the development of severe depressive disorders and comorbidities, and subsequent suicidal behaviour, and facilitate recovery from mental ill-health [42,45]. ‘Mates in Construction’, a large-scale intervention in the construction sector in Australia, has demonstrated acceptability and effectiveness of a mental health promotion intervention in increasing suicide awareness, sign-posting to relevant support, and help-seeking behaviours [26]. Despite these facts, only 7% of mental health promotion and prevention programmes globally are workplace-based [46].

Workplace interventions directed at both the organisational level and individual level have been shown to result in positive outcomes [45,47], by preventing mental ill-health and by improving job performance [48]. Research indicates that the implementation of workplace mental health interventions may be successful in SMEs [49]. Workplace interventions that adopt an organisational approach, whereby action occurs by management, may have significant, positive effects on mitigating burnout [50,51,52,53,54], decreasing anxiety [55], and alleviating feelings of stress [56,57]. Research shows that management needs to be involved in fitting the intervention into the existing organisation goals, policies, and infrastructure [58]. This can be facilitated through the implementation of a local ‘champion’ to ensure that the intervention fits into the organisation, and importantly, to encourage engagement with the intervention [59]. Action from management targets the psychosocial workplace factors that directly impact on stress, burnout, depressive symptoms, and anxiety symptoms [60]. Mental health promotion should not only be implemented top down via management, but also bottom up, targeting individuals within the organisation [61].

The literature indicates that workplace interventions should be tailored to the resources and needs of the workplace to increase efficacy [62]. This includes employees in planning and implementation to improve the ownership and acceptability of the intervention [63]. Complex workplace interventions require continuous observation, reflection, and adaptation to the implementation strategy in order to be successful [64], therefore a rigid standardised implementation process is not feasible or recommended. While a standardised process may be helpful from a research perspective, its practicality is limited for future generalisability to other settings. At present, there is no known workplace-based intervention that targets mental ill-health on the spectrum of non-clinical to clinical symptoms, and that focuses on each level of the organisation to maximise effectiveness.

Workplace mental health promotion interventions applicable to individuals, groups, and whole populations can be delivered through media and communication technologies [65] and individuals who engage with a mental health intervention regularly can experience improvements in relation to feelings of work stress, and well-being, with lasting effects [66]. Unguided, web-based interventions have also been shown to be effective in improving symptoms of mild/subthreshold depression [67]. The use of digital interventions also has the potential for increased reach, particularly in the context of sectors that have inflexible shift patterns and busy workloads (i.e., healthcare), and that have employees working on various sites (i.e., construction) [68].

The EU Horizon 2020 project Mental Health Promotion and Intervention in Occupational Settings (MENTUPP) is a timely initiative. MENTUPP is a comprehensive, multilevel intervention targeting both clinical mental disorders (depression and anxiety disorders), non-clinical mental health problems (stress, burnout, depressive symptoms), and stigma related to mental health in the workplace. The multilevel intervention adopts the framework to create more mentally healthy workplaces by Petrie et al. [69] and is targeted at the individual level (e.g., providing coping strategies, psychoeducation), group level (e.g., peer-support and de-stigmatisation), the supervisor level (e.g., encouraging help-seeking, addressing psychosocial risks in the work environment), and the organisational level (e.g., promoting positive work environments) [69]. The framework encompasses primary prevention for healthy workers, secondary prevention for symptomatic or at-risk workers, and tertiary prevention for workers with mental illness. The MENTUPP intervention applies an integrated approach to workplace mental health through (i) protecting mental health by reducing work-related and other risk factors for mental health problems, (ii) promoting mental health by developing the positive aspects of work as well as worker strengths and positive capacities, and (iii) responding to mental health problems as they manifest at work regardless of cause (work-related or otherwise) [69]. It addresses leaders and HR staff as gatekeepers, all employees and leaders that are suffering from depression, anxiety or reduced wellbeing or are at-risk for mental ill-health, and the local culture at the SME to promote a healthy working environment and to combat stigma against depression and mental ill-health. The development of an integrated intervention approach such as MENTUPP is likely to achieve maximum mental health benefits, given that organisational changes may result in sustainable transformations in the workplace in addition to addressing mental health issues at an individual level [70] and that employee mental health cannot be viewed in isolation from the workplace psychosocial environment [71]. Becoming active on all levels of intervention with sufficient intensity can stimulate synergistic and catalytic effects in multilevel interventions [72].

Given that interventions are hypothesized to be more successful when tailored to the characteristics of those engaging with them [73], the materials developed for the MENTUPP intervention are tailored to the construction, healthcare, and ICT sectors with a focus on the work-related factors and problems experienced. Intervention materials will be available to employees and managers/owners of SMEs through an online platform known as the MENTUPP Hub where users can self-navigate through the tailored interventions. The materials consist of psychoeducational material delivered via online written materials and videos as well as reflective and practical exercises. Research indicates that psychoeducational interventions can reduce symptoms of depression, anxiety, and psychological distress by informing individuals what actions they can take to prevent, intervene, and treat their symptoms [74], and may offer a first-step intervention to individuals experiencing psychological distress or depression [75]. A variety of methods will be employed to deliver the materials, such as online written materials, videos, audio clips, and reflective and practical exercises, to enhance the usability and acceptability of the Hub for all users [76]. The primary aim of the MENTUPP intervention is to improve mental health and mental wellbeing in the workplace, with a secondary aim of reducing depression and suicidal behaviour by providing tailor-designed mental health promotion materials for the construction, healthcare, and ICT sectors.

The central aim of the pilot study will be to examine the feasibility, acceptability, and uptake of the MENTUPP intervention across target SMEs. This paper describes the protocol for conducting the pilot study. The findings will allow for optimisation of the MENTUPP intervention, implementation, and evaluation in function of the cluster randomised controlled trial (cRCT).

The specific objectives of the pilot study will be to:○Evaluate the delivery of the interventions via the MENTUPP Hub;○Evaluate the procedures and instruments that will be used to evaluate the MENTUPP intervention;○Examine the implementation strategy of the MENTUPP intervention;○Estimate parameters required in the power calculations for the MENTUPP cRCT.

## 2. Materials and Methods

### 2.1. Study Design

This pilot study will involve both quantitative and qualitative measures to evaluate the delivery of the MENTUPP intervention and relevant tailored materials in the construction, healthcare, and ICT sectors, and within each country using colloquial and everyday language of the intervention country. The study design will be a non-randomised, uncontrolled pre- and post-intervention process evaluation (and preliminary outcome evaluation). MENTUPP is a complex, multilevel intervention [77,78,79] which entails multiple sources of data collection (surveys, a monitoring instrument, log data of users, and focus groups with leaders, employees, and local research officers responsible for implementing the MENTUPP intervention in the intervention countries) to examine the delivery and implementation of the intervention in different organisational and cultural settings. This study represents one aspect (feasibility and piloting) of the broader MENTUPP project which aims to develop, implement, and evaluate a workplace-based, mental health promotion intervention (see Figure 1).

### 2.2. Study Population

#### 2.2.1. Organisation Level

Nine countries will participate in the pilot study and each country will recruit at least one SME from a specific sector. This will be as follows: construction—Albania, Australia, and Ireland; health—Hungary, Kosovo, and The Netherlands; ICT—Finland, Germany, and Spain. Local research officers in each country will recruit one or more SMEs for their specified sector and this will be guided by what is most practical (e.g., approaching an SME with which they already have links, connecting with representatives by establishing a connection with workers’ groups, etc.). A small sized enterprise is defined as an enterprise with between 10 and 50 employees and a medium sized enterprise consists of 50–250 employees [80]. Definitions and inclusion criteria of the construction, health, and ICT sectors are based on NACE guidelines [81]. Construction SMEs include companies involved in site preparation, building of complete structures or parts thereof, civil engineering works, as well as those involved in sub-contracting, materials supply, professional design, engineering, etc. For the pilot study, the focus on healthcare SMES will be on residential care facilities. ICT SMEs are those involved in computer programming, consultancy and related activities, information service activities, and telecommunications.

SMEs will be deemed eligible for the intervention if they agree to predetermined criteria: (1) allocating a local champion to the project, (2) creating a project planning group within the SME with at least one employee and one member of management, (3) allowing employees at least eight hours over six months to use the MENTUPP Hub, and (4) actively and regularly promotion the intervention with employees.

#### 2.2.2. Individual Level

Participants will be deemed eligible for the intervention if they are: (1) full- or part-time employees or either contractors, managers/supervisors, or both, including individuals on sick leave or other types of authorised leave (e.g., maternity leave, care leave); (2) working within an SME in the construction/healthcare/ICT sector; (3) are aged 18 years or older; and (4) are willing to give their informed consent to the study.

#### 2.2.3. Sample Size

One of the aims of this pilot study is to estimate the level of attrition expected in the cRCT [79]. Each of the nine intervention countries will recruit 1–3 SMEs in one of the three sectors (construction/healthcare/ICT) aiming to recruit approximately 60–70 participants (employees and managers) in each intervention country. This sample size allows for an attrition rate of 62–67%, ensuring at least 23 complete sets of data across the intervention (pre- and post-intervention) within each country. With a sample of approximately 600 participants and accounting for 60% attrition, the 95% confidence interval for those lost to post-intervention would be 56–64%, i.e., a margin of error of 4%.

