#### 2.8.2. Data Protection

Personal data, including participant name, will be collected to ensure a record is kept of all participants who give their informed consent to participation in the research study. However, personal data, including participant name, will be stored separately from the evaluation data they provide, will not be shared with third parties, or appear in any reports. Each participant will have a unique identification code which is the combination of responses to four personal questions which is generated to ensure data will be kept as confidential as possible [41]. It will be used (1) to link the user activity data with the evaluation data; (2) to link participant data from different time points; and (3) to ensure accuracy in the dataset by allowing the participant to access, correct, or withdraw any data that they submit to the study. Informed consent will also be recorded in compliance with GDPR. Data will be controlled and managed by MENTUPP consortium members based at KU Leuven.

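### Recruiting 60–70 per country does not ensure 23 complete pre/post sets: the 62–67% tolerance is a break-even figure with no reserve, and 23 can be missed even at the planned 60% attrition

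*Protocol article*

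**What the plan says.** Section 2.2.3 (Sample Size) sets the target as "aiming to recruit approximately 60–70 participants (employees and managers) in each intervention country", drawn from 1–3 enterprises per country. It then states: "This sample size allows for an attrition rate of 62–67%, ensuring at least 23 complete sets of data across the intervention". The requirement applies country by country: "pre- and post-intervention) within each country". Section 2.2.1 fixes the number of countries: "Nine countries will participate in the pilot study and each country will recruit at least one SME from a specific sector".

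The same sample-size section plans on a specific loss rate, "With a sample of approximately 600 participants and accounting for 60% attrition", and gives the resulting precision: "the 95% confidence interval for those lost to post-intervention would be 56–64%, i.e., a margin of error of 4" percentage points. It opens by saying that the level of attrition is one of the things the pilot is meant to estimate.

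A complete set needs a baseline record and a six-month record that can be joined. Section 2.6 says participants create their own identifier. Section 2.8.2 says how: "Each participant will have a unique identification code which is the combination of responses to four personal questions", and lists linking data from different time points among its uses.

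**The concern.** A tolerance found by dividing the required number by the number recruited tells the team at what loss rate it would *on average* just reach the requirement. It has no margin for chance variation, for differences between countries or enterprises, or for records that are returned but cannot be joined. Presenting it as something that secures 23 in each of nine countries overstates what the design delivers. The more so because the loss rate is unknown and is itself a target of estimation.

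At stake is how the pilot is judged and used. Section 2.7 intends to interpret the data by country as well as by sector, and a reader would take 23 complete sets per country as secured. The pilot's attrition figure also goes forward to the cluster randomised trial, so it matters what that figure contains.

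**Working it through.** **Inputs.** Recruits per country n = 60–70; required complete sets 23; countries 9; planned attrition 60%; total about 600 (all from Sections 2.2.1 and 2.2.3). About 600 over nine countries is 600/9 ≈ 67 per country.

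**Step 1: reproduce the plan's figures.** Break-even attrition = 1 − 23/n.
- n = 60: 1 − 23/60 = 61.7%, stated as 62%.
- n = 70: 1 − 23/70 = 67.1%, stated as 67%.
- Pooled interval: 0.60 ± 1.96 × √(0.6 × 0.4/600) = 0.60 ± 0.039, i.e. 56.1–63.9%, stated as 56–64%.

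All stated figures reproduce.

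**Step 2: chance of 23 at the tolerance limit.** If losses are independent, the number of complete sets X is binomial (n, 1 − attrition). At exact break-even P(X ≥ 23) = 0.55 for n = 60 and 0.54 for n = 70. The chance that all nine countries reach 23 is the ninth power, about 0.004.

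**Step 3: chance of 23 at the planned 60%.** X is binomial (n, 0.4).

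| Recruits per country | Expected sets (0.4n) | P(X ≥ 23), one country | All nine (ninth power) |
|---|---|---|---|
| 60 | 24.0 | 0.65 | 0.02 |
| 65 | 26.0 | 0.81 | 0.15 |
| 67 | 26.8 | 0.86 | 0.25 |
| 70 | 28.0 | 0.91 | 0.43 |

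**Step 4: clustering of losses.** The documents give no intracluster correlation (ICC), so a range of 0.02–0.10 is assumed, with each country treated as a single cluster (beta-binomial). At 60% attrition the one-country chance becomes 0.60 down to 0.54 for n = 60, and 0.80 down to 0.66 for n = 70. With two or three enterprises in a country the effect would be smaller than this model gives.

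**Step 5: what a 90% chance requires.** Solving P(X ≥ 23) = 0.90 for attrition, with independent losses, gives 54.3% (n = 60), 57.6% (n = 65) and 60.4% (n = 70).

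**Step 6: linkage, as an assumption only.** The documents give no rate of unmatched codes. If a fraction f of returned post surveys failed to match, complete sets would be binomial (n, 0.4 × (1 − f)). At 60% non-return, f of 5%, 10% and 20% gives a one-country chance of 0.53, 0.40 and 0.18 for n = 60, and 0.84, 0.75 and 0.48 for n = 70. If unmatched returns were also counted as lost, apparent attrition would be 1 − 0.4 × (1 − f) = 62%, 64% and 68%.

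**The case against.** The best defence is that the division is right and that the sentence is an ordinary tolerance statement: if realised loss in a country is at or below the limit, 23 remain by definition. That stands as far as the arithmetic goes; there is no calculation error here. It does not rescue the word *ensuring*, because the loss rate is unknown in advance and varies by chance.

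Four stronger readings are tempting, and the documents do not support them.

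- **That the plan offers only an even chance of 23.** This holds only if true attrition sits at the tolerance limit. The plan works with 60%, below that limit, where the one-country chance is 0.65–0.91.
- **That the plan contradicts itself because its interval reaches 64% while 60 recruits tolerate only 62%.** The interval is for the pooled rate with about 600 participants. At about 67 per country the tolerance is 1 − 23/67 = 65.7%, above 64%.
- **That missing 23 breaks a rule.** No test, progression criterion or decision is tied to 23, and the Abstract uses the same number as a recruitment aim. Section 2.6 also foresees aggregation that depends on the number of cases. The nine-country probabilities therefore test the sentence as written and do not mark a point at which the pilot fails.
- **That linkage failure will be counted as attrition and bias the estimate.** Section 2.2.3 speaks of "the 95% confidence interval for those lost to post-intervention would be 56–64" per cent and does not say that an unmatched code counts as lost. Matching rules may well sit in a document not shown. The mismatch rates used above are assumptions.

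**Conclusion.** The point holds in a limited form. The 62–67% figures are correct break-even tolerances without reserve, so 23 complete sets per country is what the design expects at that limit and is not ensured. At the plan's own 60% attrition a given country reaches 23 with probability 0.65 to 0.91 (0.86 at the size implied by about 600 in total), and all nine do so with probability 0.02 to 0.43. These figures assume independent losses, one common rate in all countries, independence between countries and perfect linkage. Clustering would lower the one-country chance, by an amount that depends on an assumed ICC.

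The linkage element is secondary: a complete set does depend on a self-generated code matching across six months, and the sample-size section makes no allowance for this, but the size of any loss cannot be derived from the document. For an uncontrolled feasibility pilot this is a matter of stating correctly what the sample delivers; it does not invalidate the design.

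**What to change.** In Section 2.2.3, replace the claim that 23 sets are ensured with a statement such as: *the expected number of complete sets is 24–28 per country at 60% attrition; 23 is reached with 90% probability in a given country only if attrition is at most about 54% (60 recruited) to 60% (70 recruited)*. State that this assumes independent losses.

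Add one tabulation by enterprise and country that separates (a) post-survey non-return from (b) post surveys returned whose code matches no baseline record. Give both to the planning of the cluster randomised trial. Passing on non-return alone could under-size that trial if it uses the same code, since unmatched records also reduce usable pairs. A raw count of post surveys over recruits may also include people with no baseline record and so understate loss, which is why row (b) should be shown separately.

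The cost is a reworded sentence and one extra table. Recruitment targets and data collection are unchanged.

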Furthermore, this study employs both quantitative and qualitative data collection methods to obtain a comprehensive understanding of the reach, effectiveness, accept-ability, appropriateness, feasibility, implementation, and maintenance of the MENTUPP intervention. This evidence-based online programme is designed to target all levels of an organisation. However, it is possible that self-selection by the SMEs and further, the employees may influence the uptake and the outcomes and may understate the overall effectiveness of the intervention in the workplace setting. Self-report measures are used to capture potential changes and these may be inaccurate or incomplete. We may also be limited in our ability to assess the psychometric properties of the measures given the smaller samples for each of the languages. Furthermore, the flexible approach to implementing the intervention at this early stage of the intervention development may result in variability in how SMEs are invited and recruited (reach), and in how the intervention is implemented in the workplace (implementation). This step is necessary in learning about the various approaches to maximizing reach and to successfully implementing the intervention in the workplace, in consultation with the SMEs themselves, ahead of the cRCT. Nevertheless, considering that more research on mental health promotion in SMEs is needed, we believe that this pilot study will provide us with crucial knowledge about the needs and possibilities for improving mental health in smaller workplaces across Europe and Australia.

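### The 4-point margin for attrition assumes independent participants, but recruitment runs through only 9–27 SMEs, so it is probably too narrow for planning the cRCT

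*Protocol article*

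**What the plan says.** Section 2.2.3 (Sample Size) of the protocol article gives the purpose: "One of the aims of this pilot study is to estimate the level of attrition expected in the cRCT". On recruitment it says "Each of the nine intervention countries will recruit 1–3 SMEs in one of the three sectors", and it puts the target for each country as "aiming to recruit approximately 60–70 participants (employees and managers) in each intervention country". The precision statement takes a total of about 600 and an attrition of 60% as its starting point and concludes that "the 95% confidence interval for those lost to post-intervention would be 56–64%, i.e., a margin of error of 4" per cent.

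The section also has a separate target of at least 23 complete pre- and post-intervention data sets per country. It mentions no ICC, design effect or other allowance for clustering, and neither does the rest of the article.

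Three other places bear on the point:

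- The objectives in the Introduction include "Estimate parameters required in the power calculations for the MENTUPP cRCT".
- Section 2.2.1 requires each SME to have its own champion and planning group, to allow time on the Hub and to promote the intervention. Section 2.4 leaves each workplace free in how it promotes and uses the Hub.
- Strengths and Limitations concedes that the flexible approach "may result in variability in how SMEs are invited and recruited (reach), and in how the intervention is implemented in the workplace (implementation").

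**The concern.** A binomial interval on 600 people treats each person's dropout as unrelated to everyone else's. Here 22–67 people on average share one employer, one champion, one planning group and one way of promoting the Hub. If those shared conditions affect who completes the six-month survey, outcomes within an SME are alike and 600 people carry less information than 600 independent ones.

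The target of inference sharpens this. The interval is meant to describe attrition in a later cluster randomised trial, so it has to allow for how much SMEs differ. An interval that is too narrow would give the cRCT team false certainty about how many people to recruit.

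**Working it through.** **Inputs from section 2.2.3.** n = 600 (nine countries × 60–70 = 540–630); attrition p = 0.60; 95% two-sided; k = 9 × 1 to 9 × 3 = 9–27 SMEs. Mean SME size is m = 600/k: 66.7 for 9 SMEs, 33.3 for 18 (a middle case) and 22.2 for 27.

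**Assumed.** The article gives no ICC, so 0.02, 0.05 and 0.10 are used. SMEs are taken to be of equal size.

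**Step 1: reproduce the stated figure.** SE = √(0.6 × 0.4/600) = 0.020, or 2.0 points. The margin is 1.96 × 2.0 = 3.92 points, giving 56.1–63.9%. Wilson (56.0–63.8%) and Clopper-Pearson (56.0–63.9%) intervals agree after rounding. The printed 56–64% therefore corresponds to ICC = 0.

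**Step 2: allow for clustering.** Design effect DE = 1 + (m − 1) × ICC. Margin = multiplier × 2.0 × √DE. The multiplier is t on k − 1 degrees of freedom: 2.306 for 9 SMEs, 2.110 for 18 and 2.056 for 27. The margin with z = 1.96 is in brackets.

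| SMEs (mean size) | ICC 0.02 | ICC 0.05 | ICC 0.10 |
|---|---|---|---|
| 9 (66.7) | ±7.0 (6.0) | ±9.5 (8.1) | ±12.7 (10.8) |
| 18 (33.3) | ±5.4 (5.0) | ±6.8 (6.3) | ±8.7 (8.1) |
| 27 (22.2) | ±4.9 (4.7) | ±5.9 (5.6) | ±7.3 (6.9) |

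Worked cell, 18 SMEs at ICC 0.05: DE = 1 + 32.3 × 0.05 = 2.62; SE = 2.0 × √2.62 = 3.24 points; margin = 2.110 × 3.24 = 6.8 points; interval 53.2–66.8%.

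At ICC 0.05 the effective sample, 600/DE, is 140 (9 SMEs), 229 (18) or 291 (27).

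**Step 3: how small must the ICC be for ±4 to survive?** Take survival to mean a margin below 4.5 points and, generously, keep z. Then ICC must be below ((4.5/3.92)² − 1)/(m − 1) = 0.318/(m − 1). This is 0.005 for 9 SMEs, 0.010 for 18 and 0.015 for 27. The between-SME standard deviation of true attrition is √(ICC × 0.24), so SMEs could differ by an SD of only about 3.5 points (ICC 0.005) to 6 points (ICC 0.015).

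**Step 4: an illustration.** With one SME per country, suppose one SME of 66.7 people withdraws when 40% would have stayed. That loses 0.4 × 66.7 = 26.7 completers and moves overall attrition by 26.7/600 = 4.4 points, more than the whole stated margin. The article does not predict such a withdrawal.

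**The case against.** **The size rests on an ICC the article does not give.** This stands. The direction is well supported, but the size is conditional, and a near-zero ICC would leave ±4 intact.

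**SME conditions are partly standardised.** Section 2.2.1 makes at least eight hours of Hub time and active promotion entry conditions for every SME. Section 2.4 adds permission for use in paid hours, own-time access and weekly consortium meetings aimed at consistency. This stands in part. A reader might infer that retention depends heavily on the SME, but the article does not document that. It does document expected variability between SMEs in reach and implementation, which makes some correlation plausible.

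**The cRCT is planned in the same nine countries, so country could be a fixed stratum.** That could lower the relevant ICC, but SMEs within a country would still be clusters. With one SME per country, the two sources of variation cannot be separated.

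**The analysis method belongs in an analysis plan.** This is fair for the choice of model. It does not cover the 56–64% itself, which the article prints.

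**Little depends on the 4%.** No progression rule or hypothesis test is tied to it. A reader might also infer that attrition is the only quantity behind the sample size. That is not so: section 2.2.3 first justifies 60–70 recruits per country by the target of at least 23 complete data sets in each. Both facts lower the severity.

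**Conclusion.** The point holds as a moderate issue. The precision printed in section 2.2.3 rests on an independence assumption that the recruitment design in the same section does not support. For attrition expected in the cRCT, the interval is likely too narrow. Under the assumptions above the margin is about ±5 to ±13 points instead of ±4. Unequal SME sizes would widen it further.

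Two stronger readings are tempting and not supported. One is that the authors miscalculated: the binomial arithmetic is right. The other is that the pilot has been shown to lack the precision it claims: without a documented ICC, it can be said only that ±4 requires an ICC below about 0.005–0.015, and the article gives no basis for assuming one that low.

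**What to change.** - In section 2.2.3, state that ±4 points holds only if participants are independent, and replace it with a range. For example: allowing for clustering by SME, the margin is about ±5 to ±13 points for 9–27 SMEs and an assumed ICC of 0.02–0.10 (about ±7, or 53–67%, with 18 SMEs and ICC 0.05). Say that the ICC is assumed and that t on SMEs minus 1 degrees of freedom is used.
- Compute the reported attrition interval with SME as the cluster, and note any withdrawal of a whole SME. The choice of cluster-robust or random-effects method can be left to the analysis plan.
- Carry the clustered interval, not 56–64%, into the cRCT sample size work.

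The cost is a sentence or two and a clustered interval. No extra participants are needed, and the target of 23 complete sets per country is unaffected. The downside is a less favourable stated precision.
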